#### Secondary aim: testing predictors

Only outcomes showing significant bivariate correlations with the predictor will be included in the final multivariate logistic regression model and these selected variables will be forced into the model using enter method. For these bivariate correlations, we will use Spearman’s Rho for non-parametric data and Pearson’s r product-moment correlation coefficient for parametric data. Prior to the analysis we will check for multicollinearity, homoscedasticity, normality of the residuals as well as independence/variance of the residuals and any bias influencing the model. If these assumptions do not hold, then non-linear regression analysis will be used.

For each experiment, we will conduct multiple linear regression analysis on the entire sample to explore the predictive role of body-image flexibility (estimation of body position/size measures as inputs) on different outcomes such as interoceptive body awareness (MAIA) and sensory-processing sensitivity (HHSPS).

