S-EDE-Q†	To assess body EDs psychopathology. Self-administered questionnaire composed of 28 items using 7-point Likert scales ranging from 0 (not at all) to 6 points (markedly) about the previous 28 days. Four subscales are measured, including: dietary restraint (5 items), shape concerns (8 items), weight concerns (5 items), and eating concerns (5 items). For each subscale, the score ranges from 0 and 6 points. Participants will be grouped according to a global index score which is the average of the four subscale scores. As in Mond et al. [36], we will use a cut-off point ≥ 2.8 as clinically significant. Higher scores indicating a higher ED pathology. The S-EDE-Q have shown adequate internal consistency (Cronbach’s alpha ≥ .81 for all subscales), acceptable sensitivity (≥ 0.95), specificity (≥ 0.90), and positive (≥ 0.59) and negative (≥ 0.99) predictive values, and positive and significant correlation (≥ 0.70) with EDE diagnoses	X		
HSPS‡	To assess the tendency to process stimuli and information more strongly and deeply than others (sensory-processing sensitivity). Self-administered questionnaire composed of 27 items using 7-point Likert scales ranging from 0 (not at all) to 6 points (markedly). Five subscales are measured including: (1) sensitivity to overstimulation (9 items); (2) aesthetic sensitivity (6 items); (3) low sensory threshold (5 items); (4) fine psychological discrimination (4 items); (5) harm avoidance (3 items). For each subscale, the score ranges from 27 to 189 points. Higher scores indicate higher sensitivity level. A total global score will be obtained by averaging the five subscales. The HSPS have shown adequate internal consistency (Cronbach’s alpha ≥ 0.81 for all subscales) and construct validity in the adult Spanish population	X		

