MAIA§	To measure interoceptive body awareness. Self-administered questionnaire composed of 32 items using 6-point Likert scales ranging from 0 (never) to 5 points (always). Eight subscales are measured, including: (1) noticing (3 items); (2) not-distracting (2 items); (3) not-worrying (2 items); (4) attention regulation (7 items); (5) emotional awareness (5 items); (6) self-regulation (4 items); (7) body listening (3 items) (8) trusting (3 items). It generates a total direct score that ranges from 0 to 160 points. Higher scores indicate higher interoceptive awareness. A total global score will be obtained by averaging the six subscales. The MAIA have shown adequate internal consistency (Cronbach’s alpha 0.64 to 0.83 for all subscales)	X		
Auditory trials	Presented in four conditions: an anchor task (20 trials); a practice task (3 trials); an experimental block (30 trials) and a questionnaire block (3 trials)		X	X
Estimation of body position (finger/waist)	To assess estimation of location or position of fingertip/knuckle (allowing to calculate the estimated finger length can be calculated) and waist width after each auditory experimental trial		X	
Confidence task	It has been found that the reliability of perception might be linked to subjective rather than objective accuracy [41]. For example, previous studies using body illusions report that confidence was not accompanied by increases in objective accuracy (i.e., [42, 43]). Therefore, to assess the reliability of their estimations, after each auditory experimental trial, the feeling of confidence with the estimation of body part position will be explicitly assessed by asking the participants: “From one to seven, how confident are you of your estimation?” (7-point Likert scale)		X	X
Body feelings questionnaire (finger/waist) [25]	To assess subjective feelings about their finger/waist after the trials (susceptibility to the illusion). Participants will respond to a questionnaire containing 7-point Likert-type response items ranging from 1 (strongly disagree) to 7 (strongly agree) (Finger: 14 items; Waist: 13 items). In addition, a range of figures representing finger/waist will be presented. Each figure shows a whole hand/trunk selectively shrunk or elongated. Participants will be asked to choose one of the figures to describe the subjective feeling of the size of their finger/waist when listening to the sound. [see Additional file 2 and 3 for more details]		X	X

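### The secondary regression is specified both as logistic and as linear for numeric scores, selects variables on significance in the same data, and pools two recruited groups without a group term

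*Protocol article*

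**What the plan says.** All the model statements are in the protocol article, Statistical analyses, under Secondary aim: testing predictors.

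- Entry rule and first model: "Only outcomes showing significant bivariate correlations with the predictor will be included in the final multivariate logistic regression model". The selected variables are then forced in by the enter method.
- Checks before analysis: "multicollinearity, homoscedasticity, normality of the residuals", among others. The fallback is: "If these assumptions do not hold, then non-linear regression analysis will be used".
- Second model, next paragraph, for each experiment: "we will conduct multiple linear regression analysis on the entire sample to explore the predictive role of body-image flexibility". The inputs are given as "estimation of body position/size measures as inputs"; neither group nor EDE-Q score is listed.

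Table 1 defines the outcomes as numeric. For MAIA: "It generates a total direct score that ranges from 0 to 160 points". For HSPS: "A total global score will be obtained by averaging the five subscales". Neither is dichotomised anywhere in the article.

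The Data management section yields 12 body-estimate scores per participant: knuckle, fingertip and finger length (nine finger scores) and waist width (three), each under three sound conditions. Finger length is fingertip minus knuckle. The sample is 100, with 50 on each side of the EDE-Q cut-off. H5 posits a relationship between the body estimates and the two scores, H6 an effect of the estimates on them. Both are labelled descriptive and exploratory.

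**The concern.** Three features of one short section interact.

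1. Two incompatible models are named and nothing says which governs. A later dichotomisation of MAIA or HSPS could claim to have been pre-specified.
2. A variable reaches the final model only if it is already significant in the same data. The p-values from that model then carry much of the selection with them and cannot be read at face value. The Sample size considerations section says meaningful results will found the sample size calculation for a confirmatory study, and effects chosen for significance tend to be too large for that purpose.
3. The regression pools two groups recruited to differ in ED symptoms. If the body estimates and MAIA or HSPS both differ between groups, a pooled association partly reflects group membership. The article makes this plausible: H2 expects stronger illusions in the subthreshold group, and the secondary aim describes the two outcome constructs as related to ED.

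In addition, the fallback changes the shape of the mean function. It does not address collinear predictors, unequal variance or non-normal residuals.

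**Working it through.** The article gives no power or error figure for this analysis, so there is none to reproduce.

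**Model wording.** The outcomes are numeric, no cut is defined, and homoscedasticity and normal residuals are linear-model checks. Every element of the section except the word *logistic* points to linear regression.

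**Screen.** The text literally screens outcomes against the predictor. The calculation reads it as screening the body-estimate scores against one outcome. Inputs: n = 100; nine scores (Experiment 1) or three (Experiment 2); two-sided 0.05 (sidedness assumed); no true association.

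Chance of at least one pass with k independent scores = 1 − 0.95^k:
- k = 3: 1 − 0.8574 = 14%
- k = 9: 1 − 0.6302 = 37%

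Simulation (5,000 data sets per setting, equal correlation ρ between scores, passing scores entered into a linear model):

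| k | ρ | at least one score passes | F-test significant, given a fitted model | product |
|---|---|---|---|---|
| 3 | 0 | 13.6% | 100% | 13.6% |
| 3 | 0.5 | 12.8% | 98.0% | 12.5% |
| 3 | 0.8 | 10.0% | 80.4% | 8.0% |
| 9 | 0 | 36.4% | 100% | 36.4% |
| 9 | 0.5 | 26.5% | 91.5% | 24.3% |
| 9 | 0.8 | 16.6% | 53.8% | 8.9% |

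If all 12 scores were screened together at ρ = 0.8, 47% of fitted models would have a significant F-test. The conditional rate at ρ = 0.8 therefore runs from 47% to 80% over k = 12, 9 and 3. The last column is the share of all null data sets, per outcome, that end in a significant model; the nominal rate is 5%.

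**Redundancy.** Because length = fingertip − knuckle in each condition, the nine finger scores carry only 9 − 3 = 6 independent dimensions (matrix rank 6). Fingertip, knuckle and length of one condition cannot all enter one model.

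**Pooling.** For a 50:50 mix with no association within either group and standardised group differences d1 (body estimate) and d2 (outcome):

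r = (d1·d2/4) / √[(1 + d1²/4)(1 + d2²/4)]

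For example, 0.8/0.8 gives 0.16/1.16 = 0.14. False-positive rates are from 20,000 simulated data sets of 100. The article gives no group differences, so d1 and d2 are assumptions.

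| d1 / d2 | pooled r | false positives, no group term | with group term |
|---|---|---|---|
| 0 / 0.8 | 0 | 4.9% | 4.9% |
| 0.4 / 0.4 | 0.04 | 6.7% | 5.1% |
| 0.5 / 0.5 | 0.06 | 9.0% | 5.1% |
| 0.5 / 0.8 | 0.09 | 14.7% | 5.1% |
| 0.8 / 0.8 | 0.14 | 28.3% | 5.2% |
| 1.0 / 1.0 | 0.20 | 53.1% | 4.9% |

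**The case against.** A reader might infer that the H5 and H6 results would be invalid, or that the model cannot be fitted. The article does not support either. H5 asserts only a relationship, which the bivariate correlations answer before any model is chosen. For H6 a suitable linear model stands in the same section, and *logistic* looks like a drafting slip.

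A reader might also infer that any model fitted after the screen is bound to be significant. That holds only for uncorrelated scores. The real ones are repeated within person and linearly dependent, so the lower figures are nearer the case. The equal-correlation simulation does not reproduce their exact structure either, and screening scores rather than outcomes is one reading of ambiguous text.

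On pooling, the bias needs both variables to differ by group. H1 allows that the groups may not differ in distortion. The only effect size in the article is 0.4, cited as a conventional benchmark; if both differences were that size, the false-positive rate would be 6.7%. A whole-sample association is a legitimate exploratory quantity, and the planned group comparisons and EDE-Q correlations would help a reader judge the risk. Covariates may also be listed in a fuller plan that is not shown.

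These points stand and limit the severity. They do not remove the contradiction between the two models or the significance-based entry rule, both of which are stated rules. The exploratory label does not cure the latter, because the plan itself makes significance the gate.

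**Conclusion.** The point holds in a limited form.

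- **Certain from the text:** two incompatible models are named for numeric outcomes, and entry depends on significance in the same data.
- **Size of the selection problem:** with nine finger scores and no true association, about 37% (independent) to 17% (correlation 0.8) of data sets yield a model, and 100% to 54% of those models have a significant F-test. The H6 p-values cannot be read at face value.
- **Conditional:** without a group term the false-positive rate is 5% if either group difference is zero, 7% to 9% at differences of 0.4 to 0.5 SD on both variables, and 28% to 53% at 0.8 to 1.0 SD. The upper values are not a forecast, because the article gives no group differences.
- **Not affected:** H5, as far as the model wording and the selection go.

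This should be fixed, but it is not critical: the aim is secondary and exploratory, and no primary result depends on it.

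**What to change.** Reword the section as follows.

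1. Delete *logistic* and state multiple linear regression for MAIA and for HSPS, separately for each experiment.
2. Drop the significance screen.
3. For each experiment and outcome, pre-name a small set of non-redundant predictors built from the scores in Data management, for example the ascending-minus-descending difference in finger length (Experiment 1) and in waist width (Experiment 2). Never enter fingertip, knuckle and length of one condition together.
4. Add group, or the EDE-Q global score, as a term, and report the unadjusted association beside it, since the two answer different questions.
5. Report coefficients with 95% confidence intervals, labelled exploratory.
6. Where residual assumptions fail, use heteroscedasticity-robust or bootstrap standard errors in place of non-linear regression. Collinearity is dealt with by step 3.

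Cost: a reworded paragraph, a definition for the difference scores (the article now has only condition-level scores) and one degree of freedom per model. No new data are needed.

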## Conclusions

Accumulated evidence points towards the need for a better understanding of what aspect of perceptual processing of bodily information, including multisensory integration, is altered in EDs [19, 20]. Addressing this issue holds the potential to lay the ground for novel therapeutic interventions targeting the perceptual component of BID, which has been identified as a core feature of ED symptomatology [5]. To target this outstanding question, the present exploratory study will provide critical knowledge about the link between body perception and non-naturalistic auditory information in young normal weight females with ED symptomatology using two body illusions with different levels of emotional saliency for people EDs. The potential significance and impact of this study are noteworthy since it is still unclear whether the abnormalities in integrating auditory signals are specific to natural auditory signals related to body size or whether they extend to a general impairment related to any auditory signals. Furthermore, given that EDs treatments and body image-directed interventions still yield modest therapeutic outcomes [57–59], it is crucial to be able to identify possible predictors of individuals at high risk of developing EDs, who may potentially be targeted by specific preventive intervention such as body-image flexibility. An early identification of such young females might be the best way to reduce the incidence of EDs, as we know that EDs have a very negative prognosis and high level of relapses. From a clinical perspective, this study might pave the wave for the development of novel therapeutic approaches for BID in EDs.

An important direction for future research is to include more diverse populations with samples consisting of males and/or groups based on gender identity and sexual orientation. This would increase the external validity of the findings and allow for a more thorough examination of the factors that may influence body concerns in different populations. Additionally, future research could investigate the role of muscularity-oriented goals in body concerns, as well as any potential differences in the effects of thinness-focused goals across different populations [35–37]. Overall, this line of research has the potential to provide valuable insights into the factors that contribute to body concerns and the ways in which they may vary across different populations.

## Data Availability

The datasets generated and/or analysed during the current study will be available in the Open Science Framework.

## Abbreviations

AN: Anorexia Nervosa
BMI: Body Mass Index
BID: Body Image Disturbance
EDs: Eating Disorders
EDE-Q: Eating Disorder Examination Questionnaire
MAIA: Multidimensional Assessment of Interoceptive Awareness
HSPS: Highly Sensitive Person Scale
